**Table S2: Covariate balance: Standardized differences**

|  | | **Scotland cohort** | | **Sweden cohort** | |
| --- | --- | --- | --- | --- | --- |
|  |  | **Raw** | **Weighted** | **Raw** | **Weighted** |
| **Maternal age >35 years** | | 0.16 | -0.09 | 0.07 | -0.11 |
| **Smoking during pregnancy** | | -0.01 | 0.17 | -0.05 | 0.06 |
| **Body mass index >30kg/m^2^** | | 0.21 | -0.14 | 0.48 | 0.03 |
| **Year of delivery** | | 0.84 | -0.02 | 0.78 | -0.07 |
| **Maternal education** | | N/A | | -0.11 | -0.04 |
| **IVF pregnancy** | | N/A | | 0.03 | -0.06 |
| **Country of birth** | | N/A | | 0.14 | 0.02 |
| **Pre-existing medical condition** (chronic hypertension, renal disease, systemic lupus erythematosus) | | N/A | | -0.01 | -0.01 |
| **Chronic hypertension** | | 0.03 | -0.05 | N/A | |
| **Polycystic ovary syndrome** | | 0.07 | -0.03 | N/A | |
| **Socioeconomic status (quintiles)** | **2** | 0.02 | 0.11 | N/A | |
|  | **3** | 0.05 | 0.01 |  |  |
|  | **4** | -0.10 | 0.04 |  |  |
|  | **5** | 0.00 | -0.03 |  |  |

**Table S3: STROBE Statement—Checklist of items that should be included in reports of *cohort studies***

|  | Item No | Recommendation | Page No |
| --- | --- | --- | --- |
| **Title and abstract** | 1 | (*a*) Indicate the study’s design with a commonly used term in the title or the abstract | 1 |
|  |  | (*b*) Provide in the abstract an informative and balanced summary of what was done and what was found | 4 |
| Introduction | | | |
| Background/rationale | 2 | Explain the scientific background and rationale for the investigation being reported | 6 |
| Objectives | 3 | State specific objectives, including any prespecified hypotheses | 7 |
| Methods | | | |
| Study design | 4 | Present key elements of study design early in the paper | 7 |
| Setting | 5 | Describe the setting, locations, and relevant dates, including periods of recruitment, exposure, follow-up, and data collection | 7 |
| Participants | 6 | (*a*) Give the eligibility criteria, and the sources and methods of selection of participants. Describe methods of follow-up | 7-8 |
|  |  | (*b*) For matched studies, give matching criteria and number of exposed and unexposed |  |
| Variables | 7 | Clearly define all outcomes, exposures, predictors, potential confounders, and effect modifiers. Give diagnostic criteria, if applicable | 9  Appendix |
| Data sources/ measurement | 8* | For each variable of interest, give sources of data and details of methods of assessment (measurement). Describe comparability of assessment methods if there is more than one group | Appendix |
| Bias | 9 | Describe any efforts to address potential sources of bias | 9, 20 |
| Study size | 10 | Explain how the study size was arrived at | 7 |
| Quantitative variables | 11 | Explain how quantitative variables were handled in the analyses. If applicable, describe which groupings were chosen and why | 10-11 |
| Statistical methods | 12 | (*a*) Describe all statistical methods, including those used to control for confounding |  |
|  |  | (*b*) Describe any methods used to examine subgroups and interactions |  |
|  |  | (*c*) Explain how missing data were addressed | 10-11 |
|  |  | (*d*) If applicable, explain how loss to follow-up was addressed |  |
|  |  | (*e*) Describe any sensitivity analyses |  |
| Results | | |  |
| Participants | 13* | (a) Report numbers of individuals at each stage of study—eg numbers potentially eligible, examined for eligibility, confirmed eligible, included in the study, completing follow-up, and analysed | 12  Figure 1 |
|  |  | (b) Give reasons for non-participation at each stage |  |
|  |  | (c) Consider use of a flow diagram |  |
| Descriptive data | 14* | (a) Give characteristics of study participants (eg demographic, clinical, social) and information on exposures and potential confounders | 12, 13 (Table 1) |
|  |  | (b) Indicate number of participants with missing data for each variable of interest |  |
|  |  | (c) Summarise follow-up time (eg, average and total amount) |  |
| Outcome data | 15* | Report numbers of outcome events or summary measures over time | 15  (Table 2) |

| Main results | 16 | (*a*) Give unadjusted estimates and, if applicable, confounder-adjusted estimates and their precision (eg, 95% confidence interval). Make clear which confounders were adjusted for and why they were included | 15  (Tables 2, 3) |
| --- | --- | --- | --- |
|  |  | (*b*) Report category boundaries when continuous variables were categorized |  |
|  |  | (*c*) If relevant, consider translating estimates of relative risk into absolute risk for a meaningful time period |  |
| Other analyses | 17 | Report other analyses done—eg analyses of subgroups and interactions, and sensitivity analyses | 14 |
| Discussion | | | |
| Key results | 18 | Summarise key results with reference to study objectives | 18 |
| Limitations | 19 | Discuss limitations of the study, taking into account sources of potential bias or imprecision. Discuss both direction and magnitude of any potential bias | 19-20 |
| Interpretation | 20 | Give a cautious overall interpretation of results considering objectives, limitations, multiplicity of analyses, results from similar studies, and other relevant evidence | 18-20 |
| Generalisability | 21 | Discuss the generalisability (external validity) of the study results | 20 |
| Other information | | | |
| Funding | 22 | Give the source of funding and the role of the funders for the present study and, if applicable, for the original study on which the present article is based | 2 |

*Give information separately for exposed and unexposed groups.

**Table S4: Relationship between metformin use (multiple scripts) and preeclampsia in Scottish nulliparous singletons with diabetes**

|  | **Multiple (≥2) metformin scripts filled (N=637)** | **Metformin unexposed**  **N= 2,672** | **Crude RR**  **(95% CI)** | **Inverse probability weighted RR (95% CI)** |
| --- | --- | --- | --- | --- |
| Hypertensive disorders of pregnancy | 43 (6.8) | 209 (7.8) | 0.86 (0.63-1.18) | 0.96 (0.61-1.49) |
| Preeclampsia | 18 (2.8) | 77 (2.9) | 0.98 (0.59-1.63) | 0.96 (0.47-1.95) |
| Preterm preeclampsia <37/40 | 4 (0.6) | 30 (1.1) | 0.47 (0.16-1.39) | 0.56 (0.18-1.73) |
| Pregnancy-induced hypertension | 25 (4.0) | 132 (5.1) | 0.79 (0.52-1.21) | 0.96 (0.53-1.75) |

**Additional File 1: Analysis plan for investigating associations between metformin use in pregnancy and preeclampsia among women with diabetes**

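### Table S4: the crude RR printed for preterm preeclampsia, 0.47 (0.16-1.39), does not follow from the row's own counts, which give 0.56 (0.20-1.58)

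*SAP*

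**What the plan says.** Table S4 of the SAP appendix reports results for nulliparous singleton pregnancies with diabetes in Scotland. The exposed column is headed "Multiple (≥2) metformin scripts filled (N=637"), and the unexposed column has N = 2,672. Each row gives events and percentages by group, a crude RR with 95% CI, and an inverse probability weighted RR with 95% CI.

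The row at issue is "Preterm preeclampsia <37/40 | 4 (0.6) | 30 (1.1) | 0.47 (0.16-1.39) | 0.56 (0.18-1.73").

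The other rows are:
- Hypertensive disorders of pregnancy: "43 (6.8) | 209 (7.8) | 0.86 (0.63-1.18) | 0.96 (0.61-1.49").
- Preeclampsia: "18 (2.8) | 77 (2.9) | 0.98 (0.59-1.63) | 0.96 (0.47-1.95").
- Pregnancy-induced hypertension: "25 (4.0) | 132 (5.1) | 0.79 (0.52-1.21) | 0.96 (0.53-1.75").

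The table as shown has no footnote giving a different denominator or effect measure for any row. In the analysis plan, the section on primary outcomes makes preeclampsia primary and subdivides it by gestational age at birth, including below 37 weeks. Analysis by number of scripts is listed under Additional analyses.

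**The concern.** A crude RR is fixed by four numbers, all of which the table prints. In three rows the printed RR follows from them; in the preterm row it does not. A reader cannot tell from the table whether the RR or the counts are wrong, or whether the RR belongs to a different population or measure.

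The row matters because it is a planned subdivision of the primary outcome and carries the lowest RR in the table. Someone quoting it would report a 53% crude reduction that the displayed counts do not support, and someone pooling the counts would get a different answer from someone pooling the printed RR.

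**Working it through.** **Inputs (all from Table S4).** n1 = 637, n2 = 2,672; events a (exposed) and b (unexposed) as printed.

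**Formula.** RR = (a/n1)/(b/n2), with SE of log RR = sqrt(1/a − 1/n1 + 1/b − 1/n2) and 95% CI = RR × exp(±1.96 × SE).

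**Step 1: reproduce the rows that work.**

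| Row | a, b | Recomputed RR (95% CI) | Printed |
| --- | --- | --- | --- |
| Hypertensive disorders | 43, 209 | 0.863 (0.629-1.184) | 0.86 (0.63-1.18) |
| Preeclampsia | 18, 77 | 0.981 (0.591-1.626) | 0.98 (0.59-1.63) |
| Pregnancy-induced hypertension | 25, 132 | 0.794 (0.523-1.208) | 0.79 (0.52-1.21) |

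All three agree to two decimals, so the method is the table's own.

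**Step 2: the preterm row.** 4/637 = 0.63% and 30/2,672 = 1.12%, matching the printed 0.6 and 1.1. RR = 0.00628/0.01123 = 0.559. SE = sqrt(1/4 − 1/637 + 1/30 − 1/2,672) = 0.530. CI = 0.198 to 1.582. The row should therefore read 0.56 (0.20-1.58); 0.47 (0.16-1.39) is printed.

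**Step 3: can rounding explain it?** At their rounding extremes the printed percentages allow 0.55/1.15 = 0.478 to 0.65/1.05 = 0.619. A printed 0.47 means a value below 0.475, so it is excluded.

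**Step 4: can other counts or denominators explain it?**
- Other counts: searching 1 to 59 exposed events by 1 to 299 unexposed events over 637 and 2,672, no pair gives an RR of 0.47 (0.16-1.39).
- Other denominators: the printed interval implies SE = (ln 1.39 − ln 0.16)/3.92 = 0.552, and at least (ln 1.385 − ln 0.165)/3.92 = 0.543 after allowing for rounding. A risk ratio from 4 and 30 events cannot have an SE above sqrt(1/4 + 1/30) = 0.532 on any denominators. The printed figure is therefore not a risk ratio with a Wald interval from 4 and 30 events.
- Odds ratio on the stated Ns: 0.557 (0.195-1.585), no match.
- Odds ratio on a small subset: 51 denominator pairs, from 47/180 to 88/329, reproduce the printed figure to rounding. For example, 4/63 against 30/238 gives 0.470 (0.159-1.388). The document states no such subset.

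**Step 5: size.** Crude reduction: 1 − 0.47 = 53% as printed; 1 − 0.56 = 44% on the counts. Upper limit: 1.39 as printed; 1.58 on the counts.

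**Step 6: pregnancy-induced hypertension percentages.** 25/637 = 3.92% and 132/2,672 = 4.94%, against the printed 4.0 and 5.1. The counts satisfy 43 − 18 = 25 and 209 − 77 = 132. Taking preeclampsia cases out of the denominators gives 25/(637 − 18) = 25/619 = 4.04% and 132/(2,672 − 77) = 132/2,595 = 5.09%, which round to the printed values. So do any denominators from 618 to 632 and from 2,564 to 2,613. On 619 and 2,595 the RR is 0.794 (0.523-1.207), which still prints as 0.79 (0.52-1.21).

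**The case against.** The strongest reply is that the counts and the 0.47 may both be correct, for different quantities. The printed standard error is too large for a risk ratio on 4 and 30 events but fits an odds ratio on a small subset. The subsets that work are about 7% to 14% of the exposed and 7% to 12% of the unexposed, which might be the births before 37 weeks. The number of preterm births is not given, so this stays a hypothesis. If true, it would still leave an odds ratio under a column headed as a crude RR, on a denominator that contradicts the row's own percentages. It does mean one cannot say flatly that either the counts or the RR must be wrong.

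For the same reason a reader might infer that, once corrected, weighting makes no difference (0.56 crude, 0.56 weighted). The table does not establish that: the weighted RR cannot be checked from counts and might rest on a different population or scale.

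A reader might also infer that preeclampsia cases were dropped from the pregnancy-induced hypertension row. That is plausible, but other denominators give the same percentages. Such an exclusion would be a defensible choice needing a footnote; nothing in the document obliges the weighted column to use all 637 and 2,672 women.

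Finally, Table S4 is a completed results table placed ahead of the analysis plan in the same file, covers an additional analysis, and has four exposed events. The plan's outcome analysis focuses on the doubly robust estimator, not on crude ratios. All of this stands, and it limits the weight of the point. It does not make the printed cell right.

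**Conclusion.** The crude RR and interval in the preterm preeclampsia row are wrong as labelled: the stated counts and Ns give 0.56 (0.20-1.58), not 0.47 (0.16-1.39). The agreement of counts, Ns and percentages points to the RR cell, though only the source data can settle which entry is at fault. Among the crude RRs the error is confined to this row.

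The effect is modest. The crude reduction falls from 53% to 44% and the upper limit rises from 1.39 to 1.58; both intervals include 1. This is not a headline result, no planned method depends on it, and the weighted RR is not shown to be wrong. It is a reporting error that should be corrected, not one that undermines the analysis.

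The pregnancy-induced hypertension percentages are a minor labelling inconsistency with no effect on that row's RR.

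The recomputation assumes a risk ratio with a Wald interval on the log scale, an assumption borne out by the other three rows.

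**What to change.** Re-run the preterm preeclampsia row of Table S4 from the source data, then:
- if 4/637 and 30/2,672 stand, print 0.56 (0.20-1.58) as the crude RR;
- if they do not, correct the counts, percentages and crude RR, and check the weighted RR;
- if 0.47 came from another measure or a subset, replace it with the RR on the stated Ns.

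For pregnancy-induced hypertension, either print 3.9 and 4.9 on the stated Ns, or keep 4.0 and 5.1 with a footnote giving the denominators used.

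The cost is re-running one row and adding or correcting a line of labelling. The crude figure becomes less favourable; no other analysis is affected unless the counts turn out to be wrong.

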**Research question**

Among women with diabetes, is metformin associated with a reduced likelihood of preeclampsia?

Main analysis

Overview

P–Nulliparous diabetic (gestational diabetes or Type II diabetes) women with a birth recorded in the Scottish maternity and neonatal birth record between 2009 and 2018

I–Prescription of metformin during pregnancy

C–No prescription of metformin during pregnancy

O–Hypertensive disorders of pregnancy

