**Null hypothesis**

Taking metformin during pregnancy does not affect the likelihood of developing preeclampsia among women with diabetes.

1. **Background**

Metformin is an oral hypoglycaemic agent prescribed to women in pregnancy with pre-existing Type II diabetes and gestational diabetes. It has well-described benefits for mother and neonate when used in this context [22]. Beyond diabetes, metformin has been reported to reduce the likelihood of pregnancy complications among women with polycystic ovary syndrome [23, 24], and in women with previous unsuccessful attempts at in vitro fertilisation (IVF) [25].

Compared with insulin, two meta-analyses concluded that metformin administration is associated with lower rates of preeclampsia[22], and pregnancy-induced hypertension [8]. However, in women with diabetes, studies in this area have been small. Population-based research with larger numbers could generate stronger evidence to better investigate this relationship.

The objective of this research is to determine the relationship between metformin and hypertensive disorders of pregnancy (preeclampsia, eclampsia, gestational hypertension) among women with diabetes, using a national population-based cohort from Scotland.

1. **Study population**

The population will include all nulliparous singleton pregnancies with a diagnosis of diabetes (gestational diabetes or Type II diabetes), recorded in the Scottish Morbidity Records between 2009 and 2018. The Scottish Morbidity Records hold data relating to pregnancy, delivery and perinatal outcomes for all women and infants discharged from maternity hospitals across Scotland.

Exclusion criteria:

a) Multifetal pregnancy

b) Parous women (to account for clustering)

c) Missing gestational age (which will be used to calculate gestational age at exposure)

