**Exposure**

Maternal metformin use during pregnancy will be identified through the Scottish National Prescribing Information System (PIS), which has been linked with the Scottish Morbidity Records. Metformin use will be further categorised as use ever, 0 – 12 weeks, 13 – 27 weeks, and 28 weeks onward. Metformin exposure will be assessed for timing, with only prescription prior to preeclampsia diagnosis included.

1. **Primary outcomes:**

Diagnosis of preeclampsia identified by codes O11, O14 and O15 according to the International Classification of Disease Tenth Revision.

Preeclampsia will be further classified by stratifying according to gestational age at birth; <37 weeks and <34 weeks.

Secondary outcomes:

- Gestational hypertension ICD-O13
- Neonatal birthweight: small for gestational age at birth or large for gestational age at birth (defined according to **1)** < or > 2 SD; adjusted for gestational age and offspring sex or **2)** birthweight centile calculated using GROW charts; <10^th^ percentile for SGA and >90^th^ percentile for LGA) (binary)
- Macrosomia; birthweight >4500g (binary)
- Neonatal intensive care unit admission (obtained via neonatal indicator variable)
- Major congenital abnormality (binary)
- Congenital renal anomaly (binary)
- Perinatal death (binary)
- Preterm birth

1. **Additional analyses:**

- Metformin exposure for any indication, compared to the total unexposed population (whether or not they were diagnosed with diabetes)
- It is anticipated that most women requiring metformin in pregnancy will have been prescribed this in the context of Gestational Diabetes or Type II diabetes. The main analysis has therefore been limited to diabetic women, to eliminate diabetes as a confounder
- By number of scripts filled for metformin (possibly reflects compliance)
- By dose, categorised as 1g and >1g

1. **Outline of statistical analysis**
   1. Descriptive analysis

Summary statistics of baseline characteristics of patients will be presented with mean (SD) used to describe normally distributed continuous variables, median (IQR) for skewed continuous variables, and n (%) for categorical variables. Univariate analyses will be performed for each of the variables of interest to be included in the model.

Population characteristics to be described for:

a) Overall cohort

b) Metformin exposed vs non-exposed cohort

| Characteristic | Descriptor | Total population | Metformin exposed | Metformin unexposed |

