| --- | --- | --- | --- | --- |
| **Age,** (years) | mean ±SD |  |  |  |
| **Age >35 years** | n (%) |  |  |  |
| **Body mass index** (kg/m^2^) | mean ± SD |  |  |  |
| **Body mass index >30mg/kg** | n (%) |  |  |  |
| **Ethnicity** | n (%) |  |  |  |
| **Smoking,** yes | n (%) |  |  |  |
| **Deprivation score**  1  2  3  4  5 | n (%) |  |  |  |
| **Pre-gestational disorders**  Hypertension  Cardiovascular disease  Autoimmune diseases  Diabetes  Type I  Type II  Renal disease | n (%) |  |  |  |
| **Year of birth**  2009  2010  2011  2012  2013  2014  2015  2016  2017  2018 | n (%) |  |  |  |
| **Gestational diabetes** | n (%) |  |  |  |

- 1. **Outcome analysis**

Potential estimators are (i) selection model, using inverse probability weighting (IPW); (ii) outcome model, using regression adjustment; (iii) doubly robust inverse probability weighted regression adjustment (IPWRA) models. Under correct specification, all the estimators should produce similar results. We will focus on IPWRA; selection model will be included in the IPW and outcome in regression (RA) model specification. We will combine both regression adjustment and augmented IPW in a doubly robust regression model. We will also perform RA, IPW and multivariate LR separately.

Model for exposure assignment using inverse probability weighted propensity scores derived from the logistic exposure model. Adequacy of balance achieved by PS weighting will be assessed using: (i) standardised mean difference for model covariates and variance estimates between exposure groups and (ii) propensity scores overlap. If unbalanced, we will explore measures such as: addition of interaction terms; different exposure models; use of alternate weighting structures (overlap or stabilized); and lastly propensity score-based trimming with the aim of achieving overlap if the propensity score distributions.

This will be performed for the overall cohort and then subgroup analyses will be performed.

The model will be created for each outcome with the final included covariates determined by the authorship team and informed by direct acyclic graphs (Fig S1, S2). Covariates to be considered:

1. Maternal age at delivery
2. Body mass index
3. Deprivation score
4. Ethnicity
5. Smoking status
6. Pre-existing maternal disease
7. Conception with assisted reproduction

All statistical analysis will be performed using StataSE version 17.0.

- 1. Handling of missing data

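### The unexposed group mixes insulin-treated women with women on no drug, and no covariate for treatment need or glycaemia is named, which leaves residual confounding of unknown direction

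*SAP*

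**What the plan says.** The overview under Research question sets the population as "P–Nulliparous diabetic (gestational diabetes or Type II diabetes) women with a birth recorded in the Scottish maternity and neonatal birth record between 2009 and 2018" and the comparator as "C–No prescription of metformin during pregnancy". No condition is placed on other glucose-lowering treatment.

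Insulin appears only in the Background, as the comparator in the cited evidence: "Compared with insulin, two meta-analyses concluded that metformin administration is associated with lower rates of preeclampsia".

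Under Additional analyses the SAP gives its reason for the restriction: "The main analysis has therefore been limited to diabetic women, to eliminate diabetes as a confounder". The analyses listed there cover metformin for any indication against all unexposed women, number of scripts, and dose. None divides the unexposed group.

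Under Outcome analysis the candidate covariates are maternal age, body mass index, deprivation, ethnicity, smoking, assisted reproduction and "Pre-existing maternal disease", the last left undefined. The final set is left to the authors and to causal diagrams that are not shown. Subgroup analyses are mentioned but not specified.

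The Scottish columns of Table S2 show balance for age, smoking, body mass index, year of delivery, chronic hypertension, polycystic ovary syndrome and socioeconomic quintile. There is no row for diabetes type, insulin or glycaemia.

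**The concern.** Among women who all have diabetes, the decision to prescribe metformin depends on how much treatment the disease needs. Women who need no drug and women who receive insulin without metformin sit at different points on that scale, yet both count as unexposed. If treatment need is also related to preeclampsia, the RR reflects the make-up of the unexposed group as well as any effect of metformin.

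Weighting, regression adjustment and their doubly robust combination balance only what is in the models. They give no protection against a factor that is left out. A larger cohort narrows the interval but leaves this bias in place.

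The pooled contrast also answers a different question from the metformin-versus-insulin evidence in the Background, so the result cannot be set directly beside it.

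**Working it through.** **1. The SAP's own figure.** The main RR is not in the document. The nearest figure is Table S4 (two or more scripts, Scotland): preeclampsia in 18 of 637 exposed and 77 of 2,672 unexposed women.

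- Crude RR = (18/637) / (77/2,672) = 0.0283 / 0.0288 = 0.98.
- SE of log RR = √(1/18 − 1/637 + 1/77 − 1/2,672) = 0.258.
- 95% CI = 0.981 × exp(±1.96 × 0.258) = 0.59 to 1.63.

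This agrees with the printed 0.98 (0.59-1.63). The weighted RR is 0.96 (0.47-1.95).

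**2. What an unadjusted difference in treatment need could do.** Take a true metformin RR of 1 and set the preeclampsia risk of women on no drug to 1. Let

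- g1 = relative baseline risk of women treated with metformin,
- g2 = relative baseline risk of women treated with insulin without metformin,
- q = insulin share of the unexposed group.

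Then apparent crude RR = g1 / [1 + q(g2 − 1)].

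The SAP states none of these three quantities. The ranges below are assumptions.

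| g1 | g2 | q = 10% | q = 30% | q = 50% | q = 70% | RR crosses 1 at q = (g1 − 1)/(g2 − 1) |
|---|---|---|---|---|---|---|
| 1.25 | 1.25 | 1.22 | 1.16 | 1.11 | 1.06 | only at 100% |
| 1.5 | 1.5 | 1.43 | 1.30 | 1.20 | 1.11 | only at 100% |
| 2.0 | 2.0 | 1.82 | 1.54 | 1.33 | 1.18 | only at 100% |
| 1.2 | 1.5 | 1.14 | 1.04 | 0.96 | 0.89 | 40% |
| 1.2 | 2.0 | 1.09 | 0.92 | 0.80 | 0.71 | 20% |
| 1.2 | 2.5 | 1.04 | 0.83 | 0.69 | 0.59 | 13% |
| 1.5 | 2.0 | 1.36 | 1.15 | 1.00 | 0.88 | 50% |
| 1.5 | 3.0 | 1.25 | 0.94 | 0.75 | 0.63 | 25% |

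**3. Reading the table.** With g1 above 1, the apparent RR can fall below 1 only if g2 exceeds g1. When the two drug groups share one risk (first three rows), the bias is upward at every mix. When insulin women are at higher risk (last five rows), the same null effect shows as about 0.59 to 1.36, depending on q.

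**4. The same assumptions without the drug-free women.** For metformin against insulin alone, the apparent RR under no effect is g1/g2, and q drops out. It is 1.00 in the first three rows. In the last five it is 0.80, 0.60, 0.48, 0.75 and 0.50.

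**The case against.** **The comparator fits the SAP's own question.** The research question and null hypothesis concern use against non-use, and the insulin meta-analyses are background that the SAP does not promise to replicate. This stands, and it is why the main contrast should be kept.

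**Diabetes type may be covered.** The covariates are only candidates, the causal diagrams cannot be inspected, and pre-existing maternal disease could include Type II diabetes, since the descriptive table shell lists it among pre-gestational disorders. A reader might infer that every marker of severity has been left out; the SAP does not establish that. What stands is narrower: no insulin, treatment-need or glycaemia covariate is named, and Table S2 shows no diabetes-type row for Scotland.

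**The restriction sentence is about presence of diabetes.** It follows the additional comparison with all unexposed women, diabetic or not, and explains why the main analysis is narrower. A reader might take it as a claim that severity is controlled, but it does not say so. It needs clarifying, not deleting.

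**The illustration is crude and assumed.** The planned estimator adjusts for body mass index, age and other factors that may absorb part of the difference in treatment need. This stands: the table does not estimate bias in the planned analysis.

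**Conclusion.** The point holds as one of residual confounding by treatment need. The pooled comparator follows directly from its definition, and nothing in the listed covariates or additional analyses addresses insulin use or glycaemia. Restriction to diabetes does not fill that gap.

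Direction and size are unknown. The illustrative crude RRs under no effect are 1.06 to 1.82 if the two drug groups share one baseline risk, and about 0.59 to 1.36 if insulin women are at higher risk. Both ranges rest on assumed risks and an assumed insulin share of 10% to 70%.

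A reader might go further and conclude that the RR is shown to be biased in either direction, or that the near-null results in Table S4 are produced by this mixing. The SAP supports neither. A protective bias needs insulin women to carry higher baseline risk than metformin women, and the document gives no risk by treatment.

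**What to change.** - **Keep the main contrast.**
- **Add an active-comparator analysis:** metformin versus insulin without metformin. Take insulin from the linked prescribing data (assumed to hold it). Assign each woman by the first glucose-lowering drug dispensed before preeclampsia diagnosis, so that later additions do not move her between groups.
- **Include diabetes type,** gestational versus Type II, in both the exposure and outcome models.
- **Reword the sentence under Additional analyses** to say that restriction removes confounding by presence of diabetes only.
- **Show any contrast with women on no drug as descriptive only,** labelled as confounded by treatment need. Do not exclude metformin women who later received insulin: that would select on treatment need arising after exposure began. This contrast also compares the groups whose treatment need may differ most.

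**Cost and limits.** The work is SAP wording, one further drug extraction and one further set of models. Groups will be smaller and intervals wide: Table S4 has only 18 preeclampsia events among women with two or more scripts, and its weighted interval already runs from 0.47 to 1.95. The active-comparator analysis removes dependence on the unknown mix and matches the contrast in the cited evidence. It does not remove all confounding: if insulin women are at higher baseline risk, it remains biased towards benefit (g1/g2 above), and the SAP should say so. Because the document already carries weighted results, any analysis added after results are known must be labelled post hoc.
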